**Dropout criteria**

1. The patient cannot tolerate the designated intensity of exercise training during the study;
2. Serious safety issues arise during the trial;
3. The patient develops new illnesses;
4. There are significant changes in the patient's lifestyle and dietary habits during the trial;
5. The researcher believes that further trials are not in the best interest of the participant;
6. The patient revokes informed consent.

**Premature termination of the trial**

Premature closure of a trial is to be considered if:

• There’s an insufficient recruitment rate

• The study deviates from and is not compliant with the protocol, or

• The quality of the data is insufficient.

The premature closure of a site will be decided by the coordinating investigator.

Investigators have to inform the coordinating investigator immediately when they decide not to take part in the trial any longer. The decision should be well-founded. Details on further treatment and follow-up of participants on the study have to be discussed with the coordinating investigator.

In case of the following situations, a premature termination of the trial has to be considered:

• Substantial changes in risk-benefit considerations

• New insights from other trials

• Insufficient efficacy stated in a futility analysis

• Insufficient recruitment rate

**Premature termination of trial participation**

Any individual premature termination during the training period and every premature termination of follow-up must be documented by the responsible investigator. The date, circumstances, and reason for the termination should be documented in detail.

## Sample size

This study is exploratory in nature, with the primary research indicator being the observation of any difference in plasma proteins or metabolic products after HIIT and MICT. Since there are currently no research reports comparing the proteomic or metabolomic results of HIIT and MICT, this study is based on the team's previously published research on HIIT and MICT improvements in adult fasting blood glucose, estimating a difference of 21.9 units for a certain protein or metabolic product between the two groups, with a standard deviation of 15.0 units (Yaoshan Dun, Randal J. Thomas, Joshua R. Smith et al. High-intensity interval training improves metabolic syndrome and body composition in outpatient cardiac rehabilitation patients with myocardial infarction. Cardiovascular Diabetology. 2019;18:104). With a Type I error α=0.05 and a test power of 1-*β*=0.8, the study design method selected is a 2*2 crossover trial design, with the outcome indicator type as a continuous variable. It was calculated that a total of 8 participants are needed, and considering a 20% dropout rate, 10 participants should ultimately be included. The calculations were completed using PASS 15.0.5 software.

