## Statistical methods

The Shapiro–Wilk test will be performed to determine normality for continuous variables. Descriptive statistics will be presented as mean ± SD for normally distributed continuous variables while those with a non-normal distribution as median interquartile range (IQR)..

In this study, proteomic data will be processed using Spectronaut Pulsar, with raw data files converted to a standard format by local normalization. The data will undergo pre-processing to remove low-quality spectra and to normalize signal intensities across samples. Peptide identification will be performed using the UniProt with a false discovery rate (FDR) of 0.01 to control for type I errors. Quantitative data analysis will be conducted using R, where peptide intensities will be compared across samples using *t*-test. Differential expression analysis will be performed to identify significantly regulated proteins, with a *P*-value < 0.05 and foldchange threshold of 1.2 considered statistically significant. Venn analysis will be applied to visualize shared and unique proteins between MICT and HIIT.

When comparing two group means, *t*-test will be used in an unpaired two-tailed fashion. For more than two groups, ANOVA with Bonferroni multiple comparisons test will be used. Adjusted Pearson correlation analysis will be used to assess the association between two factors. All analyses were performed using R (version 4.2.0) software. Statistical significance was set at *P*<0.05 (two-sided).

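### The alpha of 0.05 and 80% power in section 4.4 belong to one unnamed analyte in a crossover test, and cannot be verified for the analysis and primary outcome the protocol plans

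*Protocol*

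**What the plan says.** Protocol section 4.4 (Sample size) calls the study exploratory and notes that no proteomic or metabolomic comparison of HIIT and MICT has been reported. The inputs are therefore "based on the team's previously published research on HIIT and MICT improvements in adult fasting blood glucose". The title of the cited paper is "High-intensity interval training improves metabolic syndrome and body composition in outpatient cardiac rehabilitation patients with myocardial infarction". From it the section takes "estimating a difference of 21.9 units for a certain protein or metabolic product between the two groups, with a standard deviation of 15.0 units". With alpha 0.05, power 0.8, a 2x2 crossover and a continuous outcome, "It was calculated that a total of 8 participants are needed"; 20% dropout brings this to 10. The section gives neither the kind of SD nor the sidedness of the test.

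Section 4.6 (Outcomes) makes the primary outcome any plasma protein or metabolic molecule found to differ after HIIT and MICT.

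Section 4.7 (Statistical methods) declares a protein significant at P<0.05 with a fold change of 1.2, and says that for two group means the t-test "will be used in an unpaired two-tailed fashion". The false discovery rate of 0.01 there applies to peptide identification, and Bonferroni is reserved for comparisons of more than two groups. No correction across proteins is stated.

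**The concern.** Section 4.4 is the only justification for the number of participants, and a reader will take its alpha and power as properties of the trial. Three things break that link.

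- **The input.** A glucose difference and SD from outpatients after myocardial infarction stand in for an unnamed protein in healthy sedentary men aged 30-35. A crossover calculation needs the SD of within-person differences, and the text does not say whether 15.0 is that.
- **The test.** The calculation is for a crossover; the analysis text describes an unpaired test, although each man contributes to both conditions.
- **The alpha.** The calculation is for one test at 0.05; the primary outcome is a search over everything quantified.

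At stake is how the protein list is read. A protein missing from it could be taken as absent with 80% power, and a protein on it as protected by a 5% error rate. Neither has been shown.

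**Working it through.** **Inputs.** From 4.4: difference d = 21.9, SD = 15.0, alpha 0.05, power 0.80, N = 8, dropout 20%. From 4.7: two-sided, unpaired, P<0.05 per protein. Assumed, because the protocol does not give them: 100, 500 or 1000 proteins tested, and within-person correlation from 0 to 0.8.

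**Step 1. Reproduce the 8 and the 10.** Crossover t-test with N completers: noncentrality = d·√N / SD_diff, df = N−2, two-sided 0.05.
- If 15.0 is the SD of paired differences: N = 7 gives 21.9·√7/15 = 3.86 and power 0.866. Equal sequences round this up to 8: 21.9·√8/15 = 4.13, df 6, power 0.927.
- If 15.0 is the within-subject SD: SD_diff = 15·√2 = 21.2. The normal approximation gives N = ((1.960+0.842)·21.2/21.9)² = 7.36, again 8.
- Dropout: 8/(1−0.2) = 10.

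So 8 and 10 reproduce, but 8 arises from two incompatible readings of the SD.

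**Step 2. Power for the single assumed analyte, noncentral t.**

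| Reading of 15.0 and test | 8 completers | 10 completers |
|---|---|---|
| SD of paired differences, crossover test | 0.927 | 0.980 |
| Within-subject SD, crossover test | 0.684 | 0.815 |
| SD per condition, unpaired test, independent values | 0.775 | 0.870 |

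For the third row, noncentrality = 21.9/(15·√(2/8)) = 2.92 with df 14; 9 per condition would give 0.828. With the crossover test, 80% at 8 completers requires SD_diff of at most 18.4.

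**Step 3. The unpaired test on data that are really paired (simulation, 8 completers).**

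| Within-person correlation | 0 | 0.3 | 0.5 | 0.7 | 0.8 |
|---|---|---|---|---|---|
| Power, SD_diff = 15 | 97% | 93% | 84% | 60% | 37% |
| Power, within-subject SD = 15 | 78% | 64% | 49% | 25% | 12% |

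The true type I error of the unpaired test falls from 5% at correlation 0 to about 1% at 0.5 and 0.2-0.3% at 0.7.

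**Step 4. The alpha over many proteins.** Expected false positives at unadjusted P<0.05 among m unchanged proteins are 0.05·m: 5, 25 and 50 for m = 100, 500 and 1000. If the tests are independent, the chance of at least one is 1−0.95^m, which is 0.994 already at m = 100. These figures suppose a test that holds 5% per protein and come before the fold-change filter. The filter's effect cannot be computed, because the units in 4.4 have no baseline level.

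**Step 5. What a correction would cost.** Bonferroni (alpha 0.05/m), used only as an illustration, crossover test, 8 completers:

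| m | SD_diff = 15 | Within-subject SD = 15 |
|---|---|---|
| 100 | 0.134 | 0.041 |
| 500 | 0.039 | 0.010 |
| 1000 | 0.022 | 0.005 |

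With SD_diff = 15, 80% power would need 15, 18 and 20 completers.

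**Step 6. What the design can detect.** Smallest within-person difference detectable with 80% power by the crossover test, in SDs of differences:

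| Alpha | 8 completers | 10 completers |
|---|---|---|
| 0.05 | 1.19 | 1.01 |
| 0.001 (illustrative) | 2.60 | 1.97 |

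**The case against.** The calculation is not wrong. Taking 15.0 as the SD of paired differences is natural for a 2x2 crossover, and then 8 completers exceed 80%. With all 10 participants, every row of the Step 2 table exceeds 80%, so for one analyte those shortfalls appear only once dropout occurs. The section also says openly that the study is exploratory and why it borrowed glucose figures. All of this stands, and it is why this is not an arithmetic error. Eight is nevertheless the number the protocol itself ties to 80%.

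A reader might go further and infer that the planned analysis has less than 80% power. The documents do not support that as a general statement. Testing each protein at P<0.05 raises the number of false positives but does not lower the power for any one protein; the low figures in Step 5 apply only to a corrected analysis, which the protocol does not plan. The unpaired test does not always lose either: with SD_diff = 15 and correlation up to 0.5 it keeps at least 84%. For the same reason, a nearly empty corrected list is not the likely outcome of the plan as written; false positives are the more direct risk.

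The unpaired wording follows the proteomics paragraph, which itself says only that a t-test is used. A paired test may be intended for the proteins, but the text does not say so.

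**Conclusion.** The concern holds as a mismatch between the sample-size calculation and the planned analysis, and it should be fixed. The 8 and the 10 are correct for what was calculated: one analyte, one test at 0.05, a crossover. They do not carry over to an outcome of any differing protein tested as 4.7 describes. At 8 completers the single-analyte power is 0.93, 0.68 or 0.775 according to what 15.0 means and which test is used. For the unpaired test on paired data it runs from about 12% to 97%. Across the proteome, either the 0.05 is lost (no correction) or the power is (Bonferroni: 0.13 to 0.02 with SD_diff = 15). The 80% thus cannot be verified for the planned analysis and fails under several plausible readings.

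The single-analyte figures in Step 2 rest on the protocol's own inputs under each reading of the SD. The ranges rest on assumed correlations of 0 to 0.8 and assumed counts of 100 to 1000 proteins.

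**What to change.** Keep N = 10 and rewrite section 4.4 so that it:

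1. says the size is set by feasibility for an exploratory study, and withdraws the 80% power claim for the any-protein outcome;
2. states which SD 15.0 is, if the glucose figures are kept as background;
3. rests on the paired or crossover test, with 4.7 changed to name the same test;
4. reports the minimum detectable within-person difference at 80% power for 8 and 10 completers: about 1.2 and 1.0 SD of differences at alpha 0.05, and about 2.6 and 2.0 at an illustrative alpha of 0.001;
5. states that absence of a protein from the list is not evidence of no effect.

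The cost is rewording 4.4 and the matching sentence in 4.7. No participants are added. The drawback is that the stated figure becomes less favourable.

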## Interventions

**Training intervention**

**Type**: Bicycle.

**Setting**: Xiangya Hospital, Central South University, Changsha, China.

**Protocol:** A brief description of the exercise program is as follows:

- MICT: The MICT protocol consistes of a 1-minute warm-up, followed by training at 50% MEC for 36 minutes, and concluding with a 4-minute cooldown, resulting in a total exercise duration of 41 minutes.
- HIIT: The HIIT involves a 5-minute warm-up, followed by four repetitions of high-intensity training and a low-intensity recovery cycle, and ends with a 4-minute cooldown, also totaling 41 minutes. Each cycle of HIIT includes 4 minutes of high-intensity training at 70% MEC, followed by 4 minutes of low-intensity training at 30% MEC.

## Outcomes

**Primary outcome**

Any differentially expressed plasma proteins or metabolic molecules observed after HIIT and MICT.

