**Dropout criteria**

- The patient cannot tolerate the designated intensity of exercise training during the study;
- Serious safety issues arise during the trial;
- The patient develops new illnesses;
- There are significant changes in the patient's lifestyle and dietary habits during the trial;
- The researcher believes that further trials are not in the best interest of the participant;
- The patient revokes informed consent.

**Number of subjects:** N = 10

**Primary outcome:** Proteomic responses in plasma following MICT and HIIT

**Type of intervention** Exercise training

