**Evaluation and visit schedule**

**Table 1. Summary of examinations at different time-points**

| **Study Visits** | **MICT-first group** | **HIIT-first group** |
| --- | --- | --- |
| Screening (at the begining) | Medical history, physical activity habit assessment, anthropometric measurements. | |
| Visit 1 (2^nd^ week) | Cardiopulmonary exercise testing, resting ECG | |
| *Randomization* | | |
| Visit 2 (4^th^ week) | First time exercise: Venous blood will be drawn for non-specific proteomic analysis 5 minutes before exercise and 15 minutes after exercise. | |
| *Two weeks of washout period.* | | |
| Visit 3 (6^th^ week) | Second time exercise: Venous blood will be drawn for non-specific proteomic analysis 5 minutes before exercise and 15 minutes after exercise. | |

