Previous research on the mechanisms of exercise has largely centered on understanding how exercise affects specific molecules or pathways, constrained by the available research methodologies. Prior findings have demonstrated that exercise can positively influence mitochondrial quality control in both skeletal and cardiac muscles of mice. This is achieved through the activation of AMPK, which leads to improvements in insulin resistance and an enhancement in stress resistance. [8-12]. Recently, the development of multi-omics technologies and bioinformatics has provided methods to explore comprehensive exercise responses. Using these methods, researchers like Contrepois [13] and Whitham [14] have reported the acute molecular responses of healthy adults to a single session of moderate-intensity exercise. In their studies, during a single session of moderate-intensity exercise thousands of molecular changes and biological processes were revealed, including energy metabolism, oxidative stress, inflammatory responses, tissue repair, growth factor responses, and regulatory pathways. The comprehensive proteomic characteristics between different exercise intensities are not yet clear and have not been reported.

This study intends to use a crossover trial design, employing non-specific proteomics techniques and bioinformatics methods to map the molecular responses of adult plasma to MICT and HIIT. This research will be the first to explore proteins specifically and co-expressed in both forms of exercise, providing data support and direction for subsequent research in precise exercise therapy; it will also provide information for the development of exercise mimetics, allowing patients who are unable to participate in exercise due to functional impairments to also gain the health benefits associated with exercise.

**We hypothesize** that the HIIT will induce a distinctive plasma protein response in contrast to MICT.

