## Objectives

**Primary Objective**

To delineate the proteomic responses in adult plasma following MICT and HIIT.

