**Secondary outcomes**

Differences in other plasma proteins or metabolic products, based on the completion of the primary outcome measures.

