# INDIVIDUAL TRIAL PROCEDURE AND OUTCOMES ASSESSMENT

Table 2. Summary of the examinations

|  | T1 | T2 | T3 | | | T4 | T5 | | |
| --- | --- | --- | --- | --- | --- | --- | --- | --- | --- |
|  |  |  | T3A | T3B | T3C |  | T5A | T5B | T5C |
| Randomization | X |  |  |  |  |  |  |  |  |
| Demographics | X |  |  |  |  |  |  |  |  |
| Anthropometric assessment | X |  |  |  |  |  |  |  |  |
| Physical activity habit | X |  |  |  |  |  |  |  |  |
| Diet - food frequency questionnaire | X |  |  |  |  |  |  |  |  |
| Medical history | X |  |  |  |  |  |  |  |  |
| Medication history | X |  |  |  |  |  |  |  |  |
| ECG | X |  |  |  |  |  |  |  |  |
| Perceived Stress Scale | X |  |  |  |  |  |  |  |  |
| Generalized Anxiety Disorder Scale | X |  |  |  |  |  |  |  |  |
| Patient Health Questionnaire | X |  |  |  |  |  |  |  |  |
| Cardiopulmonary exercise testing | X |  |  |  |  |  |  |  |  |
| Whole blood collection, non-specific proteomics |  |  | X |  | X |  | X |  | X |
| Gas exchange parameters during exercise |  |  |  | X |  |  |  | X |  |
| Heart rate and blood pressures during exercise |  |  |  | X |  |  |  | X |  |

T1 = At enrollment (week 0); T2 = 2 weeks washout period after cardiopulmonary exercise testing (2^nd^ week); T3 = First exercise intervention (4^th^ week); T3A = 5 minutes before training; T3B = During HIIT/MICT training; T3C = 15 minutes after training; T4 = 2 weeks washout period for alternating between the two types of exercise; T5 = Second exercise intervention (6^th^ week); T5A = 5 minutes before training; T5B = During HIIT/MICT training; T5C = 15 minutes after training.

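### The primary outcome is protein-only in some sections and proteins-or-metabolites in others; no metabolite assay is planned and no contrast is fixed

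*Protocol*

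**What the plan says.** The protocol describes its primary outcome in four places.

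- Synopsis (Section 2), primary outcome entry: "Proteomic responses in plasma following MICT and HIIT".
- Section 3.2, primary objective: "To delineate the proteomic responses in adult plasma following MICT and HIIT".
- Section 4.4, Sample size: "the primary research indicator being the observation of any difference in plasma proteins or metabolic products after HIIT and MICT".
- Section 4.6, Primary outcome: "Any differentially expressed plasma proteins or metabolic molecules observed after HIIT and MICT".

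The secondary outcome in Section 4.6 is "Differences in other plasma proteins or metabolic products, based on the completion of the primary outcome measures".

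The measurement plan is proteomic. Section 3.1 describes the study as "employing non-specific proteomics techniques and bioinformatics methods to map the molecular responses of adult plasma to MICT and HIIT". Table 1 says "Venous blood will be drawn for non-specific proteomic analysis 5 minutes before exercise and 15 minutes after exercise" for both exercise visits, and the only exercise-related blood row in Table 2 is "Whole blood collection, non-specific proteomics", marked at T3A, T3C, T5A and T5C. The laboratory methods in Section 5 run from protein extraction to the database search and contain nothing for metabolites. Section 4.7 calls a protein significantly regulated at P < 0.05 with a fold-change threshold of 1.2, and displays shared and unique proteins in a Venn diagram.

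**The concern.** A primary outcome should say what is measured, which comparison is made and what counts as a result. Here the class of molecule changes between sections, and the wider class includes molecules for which no exercise-time-point assay or analysis is planned. A separate statistical analysis plan would not cure this, because the protocol itself disagrees.

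The comparison is also open. The hypothesis in Section 3.1 is that HIIT induces a response distinct from that of MICT, which calls for a test of one mode against the other. The outcome wording can be read as change after each mode separately, or as post-HIIT against post-MICT. If the first reading is followed, the hypothesis rests on a Venn overlap. A protein that crosses the threshold in one mode and just misses it in the other appears as unique to the first, although no difference between modes has been tested.

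Finally, because *any* molecule suffices, the outcome can be met by chance, and the secondary outcome has no content until the primary has been settled.

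**Working it through.** **1. Analyte class, side by side**

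| Place in protocol | Proteins | Metabolites |
| --- | --- | --- |
| Synopsis, aim and primary outcome | yes | no |
| 3.2 Primary objective | yes | no |
| 4.4 Sample size | yes | yes |
| 4.6 Primary and secondary outcomes | yes | yes |
| Tables 1 and 2, exercise blood draws | yes | no |
| Section 5, laboratory methods | yes | no |
| 4.7 Differential analysis | yes | no |

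The nearest thing to a metabolite measurement is the routine chemistry under Clinical Data in Section 5 (glucose, lipids and similar tests). It has no post-exercise time point and no row in Table 2, so it cannot supply an outcome observed after exercise.

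**2. What the stated sample size covers**

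Inputs from Section 4.4: difference 21.9, SD 15.0, alpha 0.05, power 0.80, 2×2 crossover, 20% dropout. Section 4.7 gives two-sided testing.

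Taking 15.0 as the within-subject SD, with the normal approximation:

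N = 2 × [15.0 × (1.960 + 0.842) / 21.9]² = 2 × (1.919)² = 7.4, rounded up to 8.

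With dropout: 8 / (1 − 0.20) = 10.

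The stated 8 and 10 reproduce, but for one molecule tested once at 0.05. With the noncentral t on N − 2 = 6 df, power at N = 8 is 68% if 15.0 is the within-subject SD (noncentrality 21.9 / (15√2/√8) = 2.92). It is 93% if 15.0 is the SD of the paired difference (noncentrality 21.9 / (15/√8) = 4.13).

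**3. What *any* protein at P < 0.05 implies**

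The 1% FDR in Section 4.7 concerns peptide identification. The Bonferroni step there is for comparing more than two groups. Neither corrects across proteins. The protocol does not give the number of proteins, so m is an assumption and is shown as a range.

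For m independent true nulls, the chance of at least one P < 0.05 is 1 − 0.95^m, and the expected number is 0.05 × m.

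| m (assumed) | Chance of at least one | Expected number |
| --- | --- | --- |
| 10 | 40% | 0.5 |
| 100 | 99.4% | 5 |
| 300 | over 99.999% | 15 |

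The 1.2 fold-change filter lowers these figures by an amount that the protocol does not allow one to compute. Proteins are also correlated, so independence is a simplification.

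**4. What correction costs**

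As an illustration, the power for one protein with the Section 4.4 effect at N = 8, tested at 0.05/m (noncentral t, 6 df), is:

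| m (assumed) | SD 15 within-subject | SD 15 of the difference |
| --- | --- | --- |
| 1 | 68% | 93% |
| 10 | 22% | 51% |
| 100 | 4% | 13% |
| 300 | 1.6% | 5.9% |

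These are Bonferroni figures. Benjamini–Hochberg control at 0.05 rejects everything that Bonferroni rejects and may reject more, so they are a lower bound for an FDR-controlled screen.

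**The case against.** The strongest reply is that Section 4.4 calls the study exploratory. An untargeted screen need not name one protein, its outcome can be the set of molecules that pass a rule, and Section 4.7 fixes that rule in advance. This stands as far as it goes. It does not settle which class of molecule is measured or which contrast is primary, and the same sample size section powers the trial on a single molecule.

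Four stronger readings are tempting, and the document does not support them.

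- *The two definitions are incompatible.* The proteomic outcome lies inside the wider one, and Section 4.6 joins the classes with *or*, so a proteomic result would satisfy both. They are inconsistent.
- *Metabolites can never be reported.* Section 5 stores the supernatant for later testing, so later work is possible. What is missing is a planned assay and analysis.
- *The pre-exercise samples go unused.* Tables 1 and 2 schedule them for proteomics at both sessions. A short outcome label that omits time points does not discard them.
- *Significant molecules become primary and the rest secondary.* Section 4.6 states no such rule. Its secondary outcome is vague, and that sorting is only one inference from it.

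**Conclusion.** The point holds as an inconsistency and a lack of definition in the primary outcome. The protocol alone shows three things: the analyte class differs between sections, metabolites appear in the outcomes without a matching assay or analysis, and the contrast is ambiguous. These need no assumption. The secondary outcome is not defined independently of the primary one.

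The false-positive figures rest on an assumed number of independent null proteins and ignore the fold-change filter. They show the direction and rough scale of the problem and do not estimate this trial's error rate. The stated sample size is not in dispute as arithmetic, but it describes one molecule tested once and gives no assurance about a screen of many.

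This should be corrected. The repair is mainly a matter of definition and analysis, and the scheduled samples already support it.

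**What to change.** Use one proteomic definition in the Synopsis (aim and primary outcome) and in Sections 3.2, 4.4 and 4.6.

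- **Primary:** the within-participant HIIT-versus-MICT difference in pre-to-post log2 change, across all quantified proteins, with FDR control across proteins. Section 4.7 should carry the matching analysis.
- **Secondary:** pre-to-post change within each mode. The Venn diagram can stay as a description of these results.
- **Metabolites:** delete the wording, or declare metabolomics a separate later study on stored samples.
- **Section 4.4:** state that the power figure is for one molecule tested once and does not apply to the FDR-controlled screen.

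The cost is a protocol amendment that changes the stated aim and objective as well as the outcome label, with the registry entry checked for agreement (it was not available here). No new samples or assays are needed. The real price is that, with about 8 to 10 men, fewer proteins will be declared significant.
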